**APPENDIX 6. HBB KNOWLEDGE CHECK**

Confidential

eHBB Project  
Page 1 of 2

# HBB Knowledge Check

Study ID

- |                                                                                   |                                                                                                                                                                                                                                                                                                                                     |
|-----------------------------------------------------------------------------------|-------------------------------------------------------------------------------------------------------------------------------------------------------------------------------------------------------------------------------------------------------------------------------------------------------------------------------------|
| 1. What should you do in The Golden Minute?                                       |  a. Bathe the baby
 b. Deliver the placenta
 c. Evaluate the heart rate
 d. Help a baby breathe if necessary                                                                                                                           |
| 2. To prepare for a birth                                                         |  a. You identify a helper and review the emergency plan
 b. You ask everyone but the mother to leave the area
 c. You prepare equipment only when you need it
 d. You do not need a helper                                             |
| 3 To prepare the area for delivery                                                |  a. Open all the doors and windows to get fresh air
 b. Darken the room
 c. Make sure the area is clean, warm, and well-lighted
 d. Keep the room temperature cold                                                                     |
| 4. What should you do to keep the baby warm?                                      |  a. Open all the windows
 b. Give the baby a bath after birth
 c. Place hot water bottles next to the baby's skin
 d. Place the baby skin-to-skin with mother                                                                          |
| 5. What should you do to keep the baby clean?                                     |  a. Wash your hands before touching the baby and help mother wash her hands before breastfeeding
 b. Reuse the suction device before cleaning
 c. Keep the umbilical cord tightly covered
 d. Do not touch the baby                    |
| 6. Which baby can receive routine care after birth?                               |  a. A baby who is not breathing
 b. A baby who is gasping
 c. A baby who is crying and/or breathing well
 d. A baby who is limp                                                                                                        |
| 7. Routine care for a healthy baby at birth includes                              |  a. Drying, removing the wet cloth, and bathing the baby
 b. Drying, removing the wet cloth, and positioning the baby skin-to-skin
 c. Bathing and putting clean clothes on the baby
 d. Drying and wrapping the baby in the wet cloth |
| 8. When should the umbilical cord be clamped or tied and cut during routine care? |  a. After the placenta is delivered
 b. Around 1-3 minutes after birth
 c. Immediately after the baby is born
 d. Before a baby has cried                                                                                              |
| 9. A baby is quiet, limp and not breathing at birth. What should you do?          |  a. Dry the baby thoroughly
 b. Shake the baby
 c. Throw cold water on the face
 d. Hold the baby upside down                                                                                                                          |

## Confidential

Page 2 of 2

- 
- |                                                                                                                                       |                                                                                                                                                                                                       |
|---------------------------------------------------------------------------------------------------------------------------------------|-------------------------------------------------------------------------------------------------------------------------------------------------------------------------------------------------------|
| 10. A newborn baby is quiet, limp and not crying. The baby does not respond to steps to stimulate breathing. What should you do next? |  a. Slap the baby's back
 b. Hold the baby upside down
 c. Squeeze the baby's ribs
 d. Begin ventilation |
|---------------------------------------------------------------------------------------------------------------------------------------|-------------------------------------------------------------------------------------------------------------------------------------------------------------------------------------------------------|
- 
- |                                                    |                                                                                                                                                                                                                                                                                          |
|----------------------------------------------------|------------------------------------------------------------------------------------------------------------------------------------------------------------------------------------------------------------------------------------------------------------------------------------------|
| 11. In which situation should a baby be suctioned? |  a. When a baby is crying at birth
 b. When a baby is crying but there is meconium in the amniotic fluid
 c. When you see secretions blocking the mouth and nose
 d. Before drying the baby |
|----------------------------------------------------|------------------------------------------------------------------------------------------------------------------------------------------------------------------------------------------------------------------------------------------------------------------------------------------|
- 
- |                                                       |                                                                                                                                                                                                                                             |
|-------------------------------------------------------|---------------------------------------------------------------------------------------------------------------------------------------------------------------------------------------------------------------------------------------------|
| 12. Suctioning a baby unnecessarily or frequently can |  a. Cause a baby to stop breathing
 b. Make a baby start coughing and breathing
 c. Stimulate a baby to cry
 d. Increase the baby's heart rate |
|-------------------------------------------------------|---------------------------------------------------------------------------------------------------------------------------------------------------------------------------------------------------------------------------------------------|
- 
- |                                                                                    |                                                                                                                                                                                                                                                                                                      |
|------------------------------------------------------------------------------------|------------------------------------------------------------------------------------------------------------------------------------------------------------------------------------------------------------------------------------------------------------------------------------------------------|
| 13. Which of the following statements about ventilation with bag and mask is TRUE? |  a. The mask should cover the eyes
 b. Air should escape between the mask and face
 c. Squeeze the bag to produce gentle movement of the chest
 d. Squeeze the bag to give 80 to 100 breaths per minute |
|------------------------------------------------------------------------------------|------------------------------------------------------------------------------------------------------------------------------------------------------------------------------------------------------------------------------------------------------------------------------------------------------|
- 
- |                                                                                     |                                                                                                                                                                                                                    |
|-------------------------------------------------------------------------------------|--------------------------------------------------------------------------------------------------------------------------------------------------------------------------------------------------------------------|
| 14. A baby's chest is not moving with bag and mask ventilation. What should you do? |  a. Stop ventilation
 b. Reapply the mask to get a better seal
 c. Slap the baby's back
 d. Give medicine to the baby |
|-------------------------------------------------------------------------------------|--------------------------------------------------------------------------------------------------------------------------------------------------------------------------------------------------------------------|
- 
- |                                 |                                                                                                                                                                                                                                                                                              |
|---------------------------------|----------------------------------------------------------------------------------------------------------------------------------------------------------------------------------------------------------------------------------------------------------------------------------------------|
| 15. You can stop ventilation if |  a. A baby is blue and limp
 b. A baby's heart rate is slow
 c. A baby's heart rate is normal and the chest is not moving
 d. A baby's heart rate is normal and the baby is breathing or crying |
|---------------------------------|----------------------------------------------------------------------------------------------------------------------------------------------------------------------------------------------------------------------------------------------------------------------------------------------|
- 
- |                                            |                                                                                                                                                                                                                                          |
|--------------------------------------------|------------------------------------------------------------------------------------------------------------------------------------------------------------------------------------------------------------------------------------------|
| 16. A newborn baby's heart rate should be: |  a. Faster than your heart rate
 b. Slower than your heart rate
 c. Checked before drying the baby
 d. Checked only when the baby is crying |
|--------------------------------------------|------------------------------------------------------------------------------------------------------------------------------------------------------------------------------------------------------------------------------------------|
- 
- |                                     |                                                                                                                                                                                                                                      |
|-------------------------------------|--------------------------------------------------------------------------------------------------------------------------------------------------------------------------------------------------------------------------------------|
| 17. A baby who received ventilation |  a. Needs continued observation with mother
 b. Cannot be fed
 c. Always needs advanced care
 d. Should immediately receive antibiotics |
|-------------------------------------|--------------------------------------------------------------------------------------------------------------------------------------------------------------------------------------------------------------------------------------|
- 
- |                                                                     |                                                                                                                                                                              |
|---------------------------------------------------------------------|------------------------------------------------------------------------------------------------------------------------------------------------------------------------------|
| 18. When should the bag and mask and suction device be disinfected? |  a. After every use
 b. Only when they appear dirty
 c. Weekly
 d. Once a month |
|---------------------------------------------------------------------|------------------------------------------------------------------------------------------------------------------------------------------------------------------------------|
- 
- 08/21/2018 11:47pm
- projectredcap.org
- [figure not shown]The REDCap logo, featuring a red stylized 'R' followed by the text 'REDCap' in a bold, sans-serif font.
- [name], et al. BMJ Open 2022; 11:e048506. doi: 10.1136/bmjopen-2020-048506

eHBB+mHBS/DHIS2 v.1

**APPENDIX 7. SIMULATION CHECKLISTS**

Confidential

eHBB Project  
Page 1 of 2

# BMV Skill Check

Study ID \_\_\_\_\_

Complete this evaluation with participants before they attempt the OSCE evaluations.

- Read aloud the following instructions
- Use the comments below the numbered steps to score the performance
- Note the number of steps done correctly on the first attempt
- Read the feedback from Neonatalie Advanced ipad. Do not give any other feedback.

"You are attending the delivery of a term infant. You have prepared for the birth and tested the bag, mask, and suction device. You have dried and stimulated the baby, but the baby is not breathing. Show me how you will provide ventilation."

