**Figure 3. Neonatalie Advanced Manikin (Laerdal)**

[figure not shown]

Participant performance during the simulation will be tracked using the Simulation (BMV and OSCE) Checklists by the research assistant and by the NeoNatalie Advanced simulator with standardized performance-based feedback provided to each participant. The manikin stores training data in a database that can be accessed remotely. When feasible, research assistants doing the performance and clinical observations will be blinded to the allocation of the HCPs whom they are assessing.

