## 5.5 FOLLOW UP ASSESSMENTS

Participants will have ongoing access to the mHBS platform and will be sent reminders at 1, 3, and 6 months after initial NR training to take a follow-up NR knowledge test and to again participate in standardized performance simulations of bag-mask ventilation (BMV) skills and standardized simulation performance assessments conducted by research assistants who will visit their hospital facility with the NeoNatalie Advanced Simulator.

To understand the impact of educational strategies on clinical practice, clinical observations of routine care provided by participating healthcare providers will be conducted by research assistants in participating facilities using a standardized Delivery Checklist. This includes data on newborn care at the time of delivery and resuscitation (if applicable). See attached checklist. We will also gather data regarding capacity for provision of NR within facilities (e.g., number of deliveries, availability of trained staff and NR equipment), presence/absence of HBB practice corners, and rates of NR training among HCPs). We will review delivery outcomes if available from existing databases such as the Neonatal Registry before and after the HBB training. The Neonatal Registry data will be deidentified by a staff member who is not a member of the study team before release. When possible, resuscitation debriefs will be encouraged using the resuscitation debrief form and the perinatal death audit form will be used to identify the cause of death when not specified (see attached). No identifiable patient data will be stored and study facilities and participants will be identified by only by study code number.

At the end of the 6-month follow up period, participants will be asked to complete a feedback survey, designed to capture metrics related to the accessibility and utility of VR for neonatal resuscitation initial and refresher training.

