## 3. Continue ventilation (for 1 minute)

|                                                                                | Done                     | Not done                 |
|--------------------------------------------------------------------------------|--------------------------|--------------------------|
| Ventilate to produce gentle movement of the chest with each ventilation breath |  |  |
| Ventilate at 40 breaths/minute (30-50 breaths/minute acceptable)               |  |  |

The baby's chest has stopped moving with ventilation. Show me what you would do to improve ventilation.

Confidential

| 4. Improve ventilation             | Done                     | Not done                 |
|------------------------------------|--------------------------|--------------------------|
| Reapply mask                       |  |  |
| Reposition head                    |  |  |
| Clear mouth and nose of secretions |  |  |
| Open the mouth                     |  |  |
| Squeeze the bag harder             |  |  |

Score on first attempt

Confidential

eHBB Project  
Page 1 of 2

OSCE A

Study ID

Objective Structured Clinical Evaluations (OSCEs) can be used to determine whether participants have learned the essential steps to help a baby breathe. They can be used to verify that a participant knows enough to pass the course, or also as an exercise repeated regularly for practice. Most importantly, each completed evaluation should be used as an opportunity for the participant to review and learn.

Read the case scenario aloud to the participant. Provide the prompts shown in red. Indicate the baby's response to the participant's actions using the neonatal simulator or words if using a mannequin. For example, when the participants evaluate crying, show that the baby is not crying with a simulator. Say that the baby is not crying if using a mannequin. As you observe the participant, tick the boxes "Done" or "Not Done" for each activity. Apart from giving these prompts, keep silent during the evaluation.

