After participants complete the OSCE, ask the 5 questions written below OSCE A. These questions will help the participants reflect on what actions they took and what they can do better the next time. Participants who can recognize their own mistakes will better remember the right steps to take the next time. Comment on the participant's performance only at the end of the case, after he/she has answered these 5 questions.

"I am going to read a role play case. Please listen carefully, and then show me the actions you would take. I will indicate the baby's responses, but I will provide no other feedback until the end of the case."

"You are called to assist the delivery of a term baby. There are no complications in the pregnancy. The baby will be born in less than 10 minutes. Introduce yourself and prepare for the birth and care of the baby."

|                                                                                      | Done                  | Not Done              |
|--------------------------------------------------------------------------------------|-----------------------|-----------------------|
| Identifies a helper and reviews an emergency plan.                                   |  |  |
| Prepares the area for delivery (warm, well-lighted, clean)                           |  |  |
| Washes hands                                                                         |  |  |
| Prepares an area for ventilation and checks function of bag, mask and suction device |  |  |

Prompt: After 5-7 minutes give baby to participant and say, "There is meconium in the amniotic fluid.  
The baby is delivered onto the mother's abdomen. Show how you will care for the baby."

|                   | Done                  | Not Done              |
|-------------------|-----------------------|-----------------------|
| Dries thoroughly  |  |  |
| Removes wet cloth |  |  |

Confidential

Page 2 of 2

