**Prompt: Show the baby is breathing well (cries)**

|                                                                        | Done                  | Not Done              |
|------------------------------------------------------------------------|-----------------------|-----------------------|
| Recognizes baby is crying and breathing well                           |  |  |
| Clamps or ties and cuts the cord                                       |  |  |
| Positions skin-to-skin on mother's chest and puts on the head covering |  |  |
| Communicates with mother                                               |  |  |

Use the questions below to help the participant reflect on his or her own performance and then provide feedback.

1. What happened at the birth?
2. Did you follow the Action Plan?
3. What went well and what could have gone better?
4. What did you learn?
5. What will you do differently next time?

Comments

---

Confidential

eHBB Project  
Page 1 of 2**OSCE B**

Study ID

Instructions to the facilitator: Read the below instructions for the case scenario.

"I am going to read a role play case. Please listen carefully, and then show me the actions you would take. I will indicate the baby's responses, but I will provide no other feedback until the end of the case."

"You are called to assist at the birth of 34 week (7-1/2 months) gestation baby. You have identified a helper, prepared an area for ventilation, washed your hands, and checked your equipment. The baby is born, and the amniotic fluid is clear.

Show how you will care for the baby."

|                   | Done                  | Not Done              |
|-------------------|-----------------------|-----------------------|
| Dries thoroughly  |  |  |
| Removes wet cloth |  |  |

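### Simulator feedback is read out between the BMV check and the OSCEs, and OSCE A ends with feedback, so the 6-month OSCE B score is not a clean measure of unaided retention

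*Protocol*

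**What the plan says.** The BMV Skill Check in Appendix 7 fixes the order ("Complete this evaluation with participants before they attempt the OSCE evaluations") and the feedback that follows it: "Read the feedback from Neonatalie Advanced ipad. Do not give any other feedback". The OSCE A instructions ask for silence during the case and feedback after it: "Comment on the participant's performance only at the end of the case, after he/she has answered these 5 questions". The foot of the form repeats this: "Use the questions below to help the participant reflect on his or her own performance and then provide feedback". The same instructions describe the purpose as partly educational, in that "each completed evaluation should be used as an opportunity for the participant to review and learn".

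In the body of the protocol, section 5.2 (pre-course) says performance is tracked "by the NeoNatalie Advanced simulator with standardized performance-based feedback provided to each participant", and section 5.4 (immediate post-course) says the same. Section 5.5 sends participants at 1, 3 and 6 months "to again participate in standardized performance simulations of bag-mask ventilation (BMV) skills and standardized simulation performance assessments" on the same simulator. It neither mentions feedback nor withholds it.

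Section 8 makes the 6-month evaluation primary. Section 8.1 sizes the trial on a 20-point difference in the proportion passing OSCE A and OSCE B at that visit.

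**The concern.** The trial asks what participants still know and can do six months after the course. The forms aim at unaided performance: BMV is scored on the first attempt, and the OSCE assessor gives only scripted prompts. Reading out feedback after BMV and before the OSCEs works against that aim, because OSCE B scores several of the same actions. One match is very close. BMV asks the participant to respond when the chest stops moving with ventilation, and OSCE B asks for the same thing and scores the same five corrective steps.

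Section 8 expects the arms to differ because skills fade fastest in Control. Correction on the day can change the result only for those who would otherwise fail, and under that hypothesis Control has more of them. The contrast the trial is sized on could therefore be narrowed by its own measurement procedure.

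**Working it through.** **Step 1: what is stated and what is inferred.**

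- BMV before the OSCEs: stated on the BMV form.
- Simulator read-out after BMV: stated on the BMV form. Its content is not described anywhere.
- Feedback at the end of OSCE A: stated twice on that form.
- Feedback at the 6-month visit: inferred. Sections 5.2 and 5.4 state it for earlier visits; section 5.5 is silent, but the Appendix 7 forms carry no visit restriction.
- OSCE A before OSCE B, in one session: inferred from the labels and form order.

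**Step 2: overlap of OSCE B with the other stations (row count, Appendix 7).**

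OSCE B blocks: 2 + 2 + 7 + 3 + 5 + 2 + 3 = 24 rows.

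- Shared with BMV: firm seal, effective chest movement, rate of 40 per minute, and five corrective steps = 8. 8/24 = 33%.
- Shared with OSCE A: dry, remove wet cloth, recognise not crying, stimulate = 4.
- Together: 12/24 = 50%.

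A looser match that adds moving to the ventilation area and starting ventilation gives 10/24 (42%) for BMV alone and 14/24 (58%) in total. OSCE A has no ventilation rows, so the BMV read-out bears mainly on OSCE B.

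**Step 3: the plan's own sample size.**

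Inputs from section 8.1: 83 per group, 20-point difference, one-sided, 5% overall halved to 0.025, 80% power. The control pass rate is not given. The usual pooled-variance formula for two proportions gives 82 per group at 60% vs 80%, in line with 83. Over control rates of 10% to 75% it runs from 49 to 97, the maximum being at 40% vs 60%. So 60% vs 80% is an assumption that fits the stated figure, not something the protocol says.

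Power = Φ[(d − 1.96·s0)/s1], with s0 = √[2p̄(1−p̄)/n] and s1 = √{[p1(1−p1) + p2(1−p2)]/n}.

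At 60% vs 80%, n = 83: s0 = √(2 × 0.70 × 0.30/83) = 0.0711; s1 = √[(0.24 + 0.16)/83] = 0.0694; (0.20 − 1.96 × 0.0711)/0.0694 = 0.87; power 80.9%.

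**Step 4: illustration of attenuation.**

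Assume feedback lets a fraction f of would-be failers pass, the same f in both arms: p becomes p + f(1−p), so the difference shrinks to (1−f) × 20 points.

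| f | From 60% vs 80% | Difference (points) | Power | Power from 40% vs 60% |
|---|---|---|---|---|
| 0 | 60 vs 80 | 20 | 80.9% | 73.6% |
| 0.1 | 64 vs 82 | 18 | 74.7% | 64.7% |
| 0.2 | 68 vs 84 | 16 | 67.8% | 55.8% |
| 0.3 | 72 vs 86 | 14 | 60.2% | 47.2% |

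Two other assumptions show how far the answer depends on the choice:

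- Both arms rise by 5 points (65% vs 85%): s0 = 0.0672, s1 = 0.0654, (0.20 − 0.1317)/0.0654 = 1.04, power about 85%, which is higher than with no effect.
- Control alone rises by 5 points (65% vs 80%): power about 58%.

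**The case against.** Several points on the other side stand.

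A reader might infer that participants are coached on half of OSCE B. The documents do not show this. The 50% counts rows that appear on an earlier form, and it needs the OSCE A rows and the A-then-B order. The BMV form confines feedback to the simulator read-out, and nothing says that the read-out covers the five corrective steps, which make up five of the eight BMV overlaps. Rehearsed is the right word for those rows.

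A reader might also infer that power falls from about 81% to about 58% because Control gains 5 points while VR stays at 80%. That holds one arm fixed although every arm goes through the same forms. With the same 5-point lift in Control and an equal rescue fraction in both arms (f = 0.05/0.40 = 0.125), the result is 65% vs 82.5% and power about 73%. The forms shown state no OSCE pass mark, so shared rows cannot be converted into pass rates at all.

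Finally, feedback after each evaluation is an open and uniform feature of a standardised training tool, and the protocol does not contradict itself here. That is so, but it answers a teaching purpose. It gives no reason to deliver the feedback between scored stations rather than after the last one.

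**Conclusion.** The point holds in a limited form. Feedback between BMV and the OSCEs is explicit and, by itself, precedes scoring of 8 of the 24 OSCE B rows. If OSCE A also comes first in the same session, the figure is 12 of 24. That these instructions apply at 6 months is a reasonable inference from the forms, not a statement in section 5.5. The 6-month OSCE B result then mixes retention with same-day rehearsal and correction.

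This is not a bias towards one arm, since the procedure is identical in all three. The likely direction is higher pass rates and a narrower difference, but this rests on the assumption that an equal share of would-be failers is rescued in each arm. Under that assumption, from 60% vs 80%, the loss is about 6 to 21 percentage points of power for 10% to 30% rescued. Under an equal absolute rise there is no loss. The documents cannot settle which applies, so this is a cheap improvement worth making and not a demonstrated failure of the design.

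**What to change.** Change the Appendix 7 instructions, at least for the 1-, 3- and 6-month visits and identically in all arms: score BMV, OSCE A and OSCE B in sequence without comment, then give the simulator read-out and both debriefs after the last station. State the station order explicitly, and say in section 5.5 that feedback is given at follow-up and when.

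The cost is revised form wording and an assessor briefing. No visit, sample size or analysis changes, and every participant still receives all feedback. Feedback comes slightly later than in the usual HBB flow. Two things remain: rehearsal across stations within a visit, and any refresher effect of feedback given at the 1- and 3-month visits.
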